### Secondary outcome analysis

The between-group difference in mean QuickDASH score by 3 and 6 months will be compared as above for the PP population. The between-group difference in mean EQ VAS scores on a continuous scale between 0 and 100 will be analysed by 3, 6, and 12 months and compared using LMM. The between-group difference in WBS scores between 0 and 10 points (from 6 answer options corresponding 0, 2, 4, 6, 8, and 10 points) will also be analysed by 3, 6, and 12 months and compared using LMM.

A health profile will be generated for each patient using the EQ-5D-Y descriptive system. Summary statistics will be derived, including numbers and proportions of patients reporting each level of severity in each EQ-5D-Y dimension in each visit.

Observed and patient-reported adverse events will be reported with descriptive statistics, grouping patients according to received treatment.

### Interim analyses

We plan to perform an interim analysis when 20 patients (10 in each arm) have had their 6 months follow-up. The results from the interim analysis will not be published separately but will be part of the final report.

### Handling of missing data

LMM will be used to deal with missing values, assuming the dropout mechanism is missing at random (MAR). We distinguish between item-wise missing (more than one, but not all, answers in a questionnaire are missing) and case-wise missing (all answers in a questionnaire are missing). Case-wise missing will be addressed using LMM. Incomplete questionnaires with item-wise missing will be addressed by multiple imputation, if the number of questionnaires excluded due to missing items exceeds 5%.

## Monitoring

### Trial steering committee

The authors of this protocol article comprise the trial steering committee. They are responsible for conduction of the trial at each site. Smaller day-to-day information or challenges are handled via email correspondence, mainly between the PI and local investigators. Status of the trial or other important topics are discussed at 2–3 physical or virtual meetings per year.

### Data monitoring

A data monitoring committee (DMC) is unnecessary as this is an open label trial with continuous access to all data, and the steering committee will continuously evaluate the outcomes.

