### Concealment of allocation

The local investigator, with randomization rights assigned by the principal investigator (PI), will log into REDCap and irreversibly allocate patients into one of the two treatment groups. The local investigator is responsible for providing the allocated treatment by either scheduling the patient for surgery or applying a cast (or leaving the already applied cast).

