## Blinding

It is not possible to blind the surgeon, the patient, or the parents/guardians to the treatment allocation. PROM scores and 6- and 12-month radiographs will be evaluated by persons blinded to treatment allocation and not otherwise involved in the study. Data analysis will be performed by an external biostatistician blinded to treatment allocation.

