## Data Availability

The PI is the owner of the full data set. Each site has access to its own data only.

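### The Data monitoring section lets the people who run the sites evaluate outcomes continuously with access to all data, which contradicts the Data Availability section and conflicts with the Blinding section

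*Protocol article*

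**What the plan says.** All references are to the protocol article.

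- **Data monitoring** gives the reason for having no data monitoring committee: "this is an open label trial with continuous access to all data, and the steering committee will continuously evaluate the outcomes".
- **Trial steering committee** identifies the members: "The authors of this protocol article comprise the trial steering committee". On their role it says: "They are responsible for conduction of the trial at each site".
- **Data Availability** makes the principal investigator owner of the full data set and adds: "Each site has access to its own data only".
- **Blinding** says that PROM scores and the later radiographs "will be evaluated by persons blinded to treatment allocation and not otherwise involved in the study". On the analysis it says: "Data analysis will be performed by an external biostatistician blinded to treatment allocation". Surgeon, child and parents are not blinded.
- **Concealment of allocation** describes who randomises and then acts on the result: "The local investigator is responsible for providing the allocated treatment by either scheduling the patient for surgery or applying a cast".
- **Interim analyses**: "We plan to perform an interim analysis when 20 patients (10 in each arm) have had their 6 months follow-up". The article gives no purpose, recipient or decision rule for it.
- **Protocol violation** has the only trial-level stopping rule, which concerns unexpected serious complications.
- **Sample size** and **Primary outcome analysis** keep the full 2.5% error rate and 95% confidence interval for the final 12-month comparison.

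**The concern.** Open-label treatment means that those treating a child know that child's allocation. It does not mean that anyone must know the accumulating difference between the arms. The Data monitoring section runs the two together and treats the first as a reason to permit the second. In an unblinded trial with a patient-reported primary outcome, withholding aggregate between-arm results is one of the few protections left.

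Three routes to bias follow from the article's own design.

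- **Recruitment.** Those who inform families and randomise could present the trial differently once they know which way results lean.
- **Changes of treatment.** Under Adherence to intervention, a child can move from cast to surgery but not the reverse, and the move counts as a drop-out. The lead analysis is per-protocol. A shift in how readily casted children go to surgery would change the make-up of one arm only.
- **Reporting.** QuickDASH is scored by an unblinded child, with parental help where needed, after contact with site staff.

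The planned interim adds a separate question: can it lead to a non-inferiority claim, and if so at what level?

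**Working it through.** **1. The passages side by side**

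| Question | Data monitoring | Other section | Can both be followed? |
|---|---|---|---|
| Who can see outcome data? | The committee, all data, continuously | Data Availability: each site its own data; principal investigator owns the full set | No. The principal investigator's ownership does not give the rest of the committee access |
| Who evaluates PROM scores? | The committee | Blinding: blinded persons not otherwise involved | No. The committee is neither blinded nor uninvolved |
| Who does the final analysis? | Not addressed | Blinding and Statistical methods: external biostatistician, blinded according to Blinding | Yes. The committee's access does not unblind that person |

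That committee members are local investigators is an inference. It rests on their responsibility for each site, and on the Discussion's remark that the committee represents four of five Danish regions, set against four study hospitals.

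**2. The plan's own sample size**

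Inputs from Sample size: margin 15, SD 15, one-sided 2.5%, power 80%, 20% dropout.

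- n per arm = 2 × (1.960 + 0.842)² × (15/15)² = 15.7, so 16; total 32.
- 32 / (1 − 0.20) = 40. Both figures reproduce.
- Standard error with 16 per arm = 15 × √(2/16) = 5.3 points.

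**3. What one change of treatment can do in the per-protocol set (illustration; scores assumed)**

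Suppose 16 casted children, 15 scoring 0 and one scoring 48. The arm mean is 48/16 = 3. If that child goes to surgery and leaves the per-protocol set, the mean is 0. The shift is 3 points, or 3/15 = one fifth of the margin. This shows sensitivity at this sample size; it does not predict what will happen.

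**4. Type I error, only if the interim could yield a claim**

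Let the interim have 10 per arm and the final analysis 16 per arm (after dropout) or 20 per arm (none). Let ρ be the assumed correlation between 6- and 12-month scores; the article gives none. Assume the true difference sits at the margin at both times. The two test statistics have correlation r = ρ × √(n₁/n₂). With 1.96 used at both looks, the chance that at least one crosses is 1 − Φ₂(1.96, 1.96; r).

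| ρ | Final 16 per arm: r, error | Final 20 per arm: r, error |
|---|---|---|
| 1 | 0.791, 3.9% | 0.707, 4.2% |
| 0.8 | 0.632, 4.3% | 0.566, 4.4% |
| 0.5 | 0.395, 4.7% | 0.354, 4.7% |
| 0.3 | 0.237, 4.8% | 0.212, 4.8% |

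The range is roughly 4–5% against a stated 2.5%.

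**5. If the interim cannot yield a claim**

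A false claim then needs the trial to continue and the final test to cross. P(continue and cross) ≤ P(cross) = 2.5%. Stopping for harm or futility can lower this probability but not raise it, so the final level stands without adjustment.

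**The case against.** The strongest case on the other side has five parts.

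- **No early claim is stated.** The interim section names no efficacy decision, and the only stopping rule is for safety. A boundary may also sit in the full protocol or analysis plan, which are not shown. This stands. A reader might infer that the interim, or continuous review, already breaks the 2.5% level, or that any stop based on these looks does so. The article supports neither reading. It describes no formal testing at each review, so error rates for repeated testing do not apply. It also does not say that the interim compares the arms.
- **The blinded analysis survives.** A reader might infer that the committee's access undoes it. It does not: the external biostatistician can remain blinded whatever the committee sees.
- **The bias routes are partly inferred.** The on-duty surgeon judges the indication and first mentions the trial, and the article does not place these surgeons on the committee. It does not say who decides a change from cast to surgery, and it promises efforts to avoid such changes. This limits the certainty of the routes but does not remove them.
- **Some exposure exists anyway.** Families and surgeons are unblinded by necessity, and questionnaire links go out two days before the visit, which limits influence at the moment of scoring. Non-inferiority also requires the intention-to-treat analysis to agree. These soften the reporting and per-protocol routes. They do not make aggregate between-arm knowledge harmless.
- **The committee needs data for safety.** The Harms section already sends adverse events to the principal investigator. Safety oversight does not require between-arm QuickDASH results.

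Brevity of a journal article is no answer to the core point. The access statement is positive text, and it conflicts with other positive text.

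**Conclusion.** The point holds as a contradiction with a credible route to operational bias. Data monitoring and Data Availability cannot both be followed, and Data monitoring conflicts with the Blinding section's sentence on PROM evaluation. The reason given for open access does not support it. The size of any bias cannot be computed from the document; the 3-point illustration shows only that, with about 16 evaluable children per arm, single treatment decisions can matter.

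The type I error element is conditional. The rise to roughly 4–5% needs an interim claim at an unadjusted 95% confidence interval, a true difference at the margin at both times, and a 6- to 12-month correlation between 0.3 and 1. If the interim cannot support a claim, the 2.5% level is intact.

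The wording should be corrected promptly: knowledge of between-arm results, once shared, cannot be withdrawn.

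**What to change.** 1. **Data monitoring.** Reword so that, until the last 12-month visit, the steering committee as a body sees only safety events and outcome data pooled across arms. Between-arm summaries of QuickDASH, EQ VAS and WBS are held by the external statistician. Drop open-label status as a reason for access.
2. **Blinding and Data Availability.** Reconcile both with the new wording. Site-only access is not enough by itself, because unblinded staff could tabulate their own site's outcomes by arm. State that site staff do not compile such summaries.
3. **Interim analyses.** State that the interim is limited to safety, pooled SD and data completeness and cannot support a non-inferiority claim, so that the final 2.5% level stands.

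The cost is revised wording and REDCap access rights, with no extra staff. The one real loss is that the committee gives up early sight of between-arm efficacy.

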### Protocol amendments

Update on any protocol changes during the study period will be given by the PI to all recruiting centres as well as trial participants for whom it may be relevant. Substantial modifications such as changed eligibility criteria, follow-up visits, outcomes, or statistical analysis will be registered at www.clinicaltrials.gov, and a supplementary protocol will be submitted to the Research Ethics Committee in Region Zealand.

## Dissemination

The trial protocol is preregistered at www.clinicaltrials.gov. All results from the study—both positive, negative, and inconclusive—will be published in a relevant, international, scientific peer-reviewed journal. The PI will ensure publication with authorship following the guidelines of the International Committee of Medical Journal Editors (ICMJE) as well as the Consolidated Standards of Reporting Trials (CONSORT) guidelines for the reporting of parallel group randomized trials. Results will be presented at relevant national and international conferences, e.g. the Danish Orthopaedic Association. A website, www.thecastingtrial.com, is linked to the study; all relevant material and results will be available here.

### Ethical considerations

Today, most children with displaced distal forearm fractures are treated surgically under general anaesthesia with closed reduction and pin fixation. Besides the fact that surgery and anaesthesia can be stressful for the child and family, there are risks associated with surgery. These include infection, damage to the surrounding vessels, tendons and nerves, and scar tissue formation. Re-displacements are common (up to 50%), and re-operations with re-reduction with or without pin fixation may be necessary in up to half of these cases [11, 15]. Following pin fixation, a subsequent procedure (though most often without anaesthesia) is needed to remove the pins again. The child undergoing surgery will be exposed to a relatively large amount of radiation (almost threefold higher than children being treated non-surgically) due to the use of fluoroscopy in the operating room (OR) [45, 46].

In less than 0.6% of cases, a later corrective surgery will be needed if the bone remains misaligned, regardless of surgical or non-surgical treatment [47]. However, this is particularly rare in the population included in this study, as children of this age still have a great remodelling potential.

Each child in this RCT will have a 50% chance of avoiding surgery and the associated inconveniences and potential complications. In return, some children may experience some forearm deformity which we expect is mainly a cosmetic issue and has minimal or no impact on the function. If the results of this study demonstrate non-inferiority of non-surgical treatment compared to surgical treatment, it opens up the possibility of treating up to 1800 children per year non-surgically. In summary, we believe that the disadvantages associated with perhaps having a temporarily misaligned forearm are outweighed by the benefits of avoiding surgery.

## Discussion

We aimed to assess the patient-reported functional outcome after 1 year using a PROM. Unfortunately, no PROM has been developed and validated for children with upper extremity injuries. The QuickDASH has been found a reliable and valid instrument among 8–18-year-old children with upper extremity injuries [29]. It has several advantages: (1) it is short, thus reducing time consumption; (2) a Danish translation is already available; and (3) the questionnaire is feasible for children to complete despite 1–2 challenging questions.

Regarding children, there is no definition of an MCID of the QuickDASH. We defined ourselves an MCID based on a series of adult studies, assuming it to be the same in children. Future goals should be to develop a PROM on this population and, through anchor-based approaches, define a more precise MCID.

Although our study is somewhat comparable to the CRAFFT [20] study and the Finish study by Laaksonen et al. [21], the three studies also differ in either population, intervention, and/or outcome measures. The CRAFFT study includes a similar, yet larger (*n* = 750), population regarding age and fracture types. They use stratified randomization with stratification factors including centre, fracture severity and location, and patient age. We did not use stratification for several reasons: (1) we expected girls and boys in this age to have similar remodelling capacity, (2) the study is not powered to ensure equal distribution of covariates, and (3) the steering committee represents 4 out of 5 regions in Denmark, and treatment management is almost identical across regions using the same clinical guidelines. Thus, we expect no or minimal clustering effect due to treatment differences across centres. The intervention in CRAFFT is, as in our study, non-surgical treatment compared to surgical. However, they allow also reduction under conscious sedation, which we do not in our protocol. The primary outcome is patient-reported function measured by Patient-Reported Outcomes Measurement Information System Upper Extremity (PROMIS UE) by 3 months and a wide range of secondary outcomes measured by 6 weeks to 3 years follow-up including WBS, EQ-5D-Y, VAS cosmesis, and healthcare resource use. Our primary outcome is by 12 months as this is when we expect the fractures to be remodelled enough for the forearm to have regained its normal function. In relation to CRAFFT, they have conducted a qualitative study asking patients and their parents about their experience of having the injury and their thoughts about participating in a clinical trial. We used some of the information from this qualitative study to form our protocol. For instance, we decided to give information about the study the following day instead of in the emergency room (ER) as parents explained they were not able to receive the information because the situation in the ER were too stressful. Laaksonen et al. [21] will include all 0–10-year-old children (*n* = 60), but only with overriding fractures. Their intervention is to cast the fracture after finger trap traction in order to regain forearm axis, but not dorsal displacement and shortening. Their primary outcome is active forearm rotation, flexion, and extension in injured versus uninjured forearm. Secondary outcomes include radiographs, QuickDASH, Paediatric Quality of Life Inventory (PedsQL), and overall satisfaction. Although the study by Laaksonen et al. differ most from our study and CRAFFT, we have in common to investigate the potential of fracture remodelling in younger children in order to reduce the surgical burden.

In recent years, there have been a number of initiatives regarding treatment of other medical conditions that require health care providers to adapt to new and, in some cases, considerably altered treatments. In particular, researchers have focused on health education of both health providers and patients in order to improve treatment and quality of life [48]. In relation to our study, non-surgical treatment of displaced distal forearm fractures may seem counter-intuitive to surgeons as well as patients and parents. Patient/parent education and thorough information about the benefits and risks of both surgical and non-surgical treatment are therefore essential to ensure the best conditions for shared decision making.

## Trial status

Protocol version 3, June 12, 2023. Recruitment began: August 28, 2023. Expected recruitment completion: May 2025.

## Data Availability

The PI is the owner of the full data set. Each site has access to its own data only.

## Abbreviations

AO: Arbeitsgemeinschaft für Osteosynthesefragen
AP: Antero-posterior
CI: Confidence interval
CONSORT: Consolidated Standards of Reporting Trials
CRAFFT: Children’s Radius Acute Fracture Fixation Trial
DASH: Disabilities of Arm, Shoulder and Hand
DFF: Distal forearm fracture
DMC: Data monitoring committee
GDPR: General Data Protection Regulation
HIV: Human immunodeficiency virus
HRQoL: Health-related quality of life
ICMJE: International Committee of Medical Journal Editors
IQR: Interquartile range
ITT: Intention-to-treat
LMM: Linear mixed effects model
MAR: Missing at random
MCID: Minimal clinically important difference
MeSH: Medical Subject Headings
NIM: Non-inferiority margin
OR: Operating room
PedsQL: Paediatric Quality of Life inventory
PI: Principal investigator
PP: Per protocol
PROM: Patient-reported outcome measure
PROMIS UE: Patient-Reported Outcomes Measurement Information System Upper Extremity
QuickDASH: Quick Disabilities of Arm, Shoulder and Hand
RCT: Randomized controlled trial
REDCap: Research Electronic Data Capture
ROM: Range of motion
SD: Standard deviation
SH: Salter-Harris
SPIRIT: The Standard Protocol Items: Recommendations for Interventional Trials
VAS: Visual analogue scale
WBS: Wong-Baker Faces Pain Rating Scale
WHO: The World Health Organization
